##### Lung function

Spirometry (post bronchodilator FEV_1_, post bronchodilator FVC, FEV_1_/FVC ratio), carboxyhaemoglobin test,^19^ hospitalisations within the last 12 months, number of COPD exacerbations within the last 12 months, treatments will be collected as the baseline data prior to the randomisation of participants.

##### Nutritional status

Height (Holtain stadiometer), weight (calibrated weight scale) will be measured and body mass index will be calculated. Mid upper arm circumference of the participants will be measured using a measuring tape and skinfold thickness of seven sites (triceps, mid axillary, subscapular, chest, abdominal, supra iliac and thigh measurements) of the body will be measured using a validated calliper. Triplicated measurements will be taken by the same investigator and mean value will be used for the calculation of body fat mass. Fat-free mass will be calculated using Durnin and Womersley formula.^20 21^ Body composition analysis will be assessed using bioelectrical impedance (SFB7 Impedi Med dual frequency instrument, Impedi Med Limited, Australia) and software V.5.2.4.0.^22^ Seven-day diet diary method will be used to assess the dietary history and calorie intake.

##### Disease burden

Breathlessness will be measured using MRC dyspnoea grade (5-item).^23^ The health-related quality of life related to mobility, self-care, usual activities, pain/discomfort and anxiety–depression will be measured using EuroQol Five Dimensions Five Levels (25-item).^24^ Clinical status of the airways, functional limitations and psychosocial dysfunction will be determined using Clinical COPD Questionnaire (10-item).^25^ COPD Assessment Test (8-item) will be used to determine the severity of the COPD.^26^ Modified brief pain inventory (3-item) will determine the commonly reported chest pain; Work Productivity and Activity Impairment questionnaire (8-item) will be used to measure the effect of severity of COPD and general health on work productivity and regular activities^27^ and Hospital Anxiety and Depression Scale (14-items) will be used to measure the patient’s emotional state and the presence or absence of clinically significant anxiety and depression.^28^ Sleep quality of the participants will be measured using Pittsburgh Sleep Quality Index.^29^ Disease burden will be measured as baseline data prior to the randomisation and postintervention data.

##### Exercise capacity

Following a safety assessment for absolute and relative contraindications for field walking tests,^30^ maximal exercise capacity will be assessed using the ISWT^31^ and Endurance Shuttle Walking Test (ESWT).^18^ The ISWT and ESWT also include a pretest and post-test measure of SpO_2_, blood pressure, Borg rating of breathlessness,^32^ heart rate, Borg rate of perceived exertion.^33^ The sit-to-stand test will be completed for five continuous repetitions, to measure lower limb movement and strength.^34^ All measures of exercise capacity will be measured at baseline prior to the randomisation and post intervention.

##### Physical activity

Subjective health-related physical activity will be measured with the International Physical Activity Questionnaire^35^ at baseline prior to the randomisation and post intervention.

Participants will be asked to wear an activity monitor (ActiGraph wGT3X-BT, ActiGraph, Pensacola, Florida, USA), able to detect a range of PA intensities,^36^ on the right anterior hip during waking hours for 7 days prior to attending PR (baseline) and for the 7 consecutive days prior to their discharge assessment (follow-up); taking it off for water-based activities and sleep. The collection of physical activity data will coincide with a 7 days diet diary. Printed instructions will be provided to the participants regarding how to wear the monitor.

Full accelerometry methodology is provided in table 3. Data will be processed as 60 s epoch files in ActiLife V.6.13.4 (ActiGraph). Non-wear will be defined as 60 min of consecutive zero counts with allowance for 2 min of interruptions.^37^ Adherence to wearing the monitors will be assessed by examining the proportion of participants providing valid accelerometer data across a range of valid days (≥1–7 days) and minimum wear time (≥1–12 hours) thresholds. For reported group averages, only participants providing ≥4 valid days of ≥8 hours, for both time points will be included in the analyses.^38^ Step count, time spent in different absolute intensity classifications of physical behaviours^39^ and average movement intensity (activity counts per minute) will be reported. Time spent in physical activity matching participants’ prescribed walking exercise intensity will be derived by aligning the average walking speed during the ESWT with the activity monitor counts per minute and cadence.

**Table 3 T3:** Accelerometry data collection and processing parameters

Accelerometer Model	ActiGraph wGT3X-BT (V.6.13.4; firmware V.1.9.2)
Serial number range	Twenty unique devices will be used ranging from MOS2E09190601 to MOS2E24190146 averaging six deployments per device (same serial used for baseline and follow-up wear periods)
Piezosensor orientation	Triaxial
Mode setup	Mode 29 (x, y, z, steps, lux)
Original sample rate	100 Hz (.gt3x file format)
Deployment method	Baseline: Fitted by research team on day 0 (baseline PR assessment) Fitted by participant on day 1 Follow-up: Fitted by research team day 0 (11th/12th session) Fitted by participant on day 1
Location worn	Anterior hip adjacent to the mid-line of the thigh
Requested days of wear	7 days of free living (days 1–7; 10 080 epochs)
Initialisation	Not deployed in delay mode in order to standardised capture of day 0 (00:00) with stop time based on date of first PR class (baseline) and data of discharge assessment (follow-up)
Wear instructions	Wear continuously except for sleep and water-based activities
Non-wear appropriation	≥60 min of consecutive 0 s with allowance for 2 min of interruptions were deemed biologically implausible and coded as non-wear
Valid day criteria	≥8 hours of valid waking wear time
Valid file	≥4 valid days for each of the two time points
Missing data	Data modelling or imputation will not be performed
Epoch length	60 s
Intensity classification (absolute)	Uniaxial (x-axis) cut-points as follows: sedentary time <100 cpm; light intensity 100–2019 cpm; moderate intensity 2020–5998 cpm; vigorous intensity ≥5999 cpm (moderate-to-vigorous intensity ≥2020 cpm)
Intensity classification (relative)	Uniaxial (x-axis) cut-points based on Endurance Shuttle Walk Test performance

PR, pulmonary rehabilitation.

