## Methods and analysis

### Study design and registration

The proposed study will be conducted in three phases. Phase 1: a qualitative study will be conducted to inform the adaptations required to make PR specific to the Sri Lankan context. Phase 2 is a single-blind randomised control feasibility trial. Adults living with COPD will be randomised (1:1) into adapted PR or usual care. Phase 3: qualitative evaluation of the trial to determine the feasibility and acceptability of PR deliverers and participants. The trial will be conducted, analysed and reported according to the Standard Protocol Items: Recommendations for Interventional Trials statement^12^ and trial has been registered on the ISRCTN website. Study was started on ethical approval on 24 July 2020 for phase 1 of the study. The design of the study and flow of participant enrolment is presented in figure 1.

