##### Feasibility

Measures to assess feasibility are provided in table 1 and include the comprehensive assessment of the feasibility of patient recruitment and the intervention delivery.

**Table 1 T1:** Primary outcome measures—feasibility and operational experience assessment

Feasibility of patient recruitment	Data sources
Feasibility of screening and recruiting participants	Interviews with the healthcare professionals, screening log
Suitability of the inclusion criteria	Interviews with the healthcare professionals, screening log
Number of eligible patients, number of patients screened, number of patients invited to take part, actual number of participants who consent to take part	Screening log
Number of patients who refuse, drop out and the reasons for refuse and drop out	Interviews with the patients, screening log

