### Sample size and recruitment target

This study is a feasibility trial that aims to provide data for an accurate estimation of the required sample size for future trials. Therefore, a formal sample size calculation is not required. We aim to recruit and randomise 50 participants to the study (25 in each group).

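### Baseline accelerometer averages are limited to participants who also have a valid follow-up week, so they describe retained wearers rather than those randomised (minor)

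*Protocol article*

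**What the plan says.** The Physical activity section asks for seven days of monitor wear before PR starts and again before the discharge assessment. For reported group averages it then states that "only participants providing ≥4 valid days of ≥8 hours, for both time points will be included in the analyses". In Table 3 the 'Valid file' row gives the same condition, "≥4 valid days for each of the two time points", and the 'Missing data' row adds: "Data modelling or imputation will not be performed".

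One accelerometer summary lies outside this rule: "Adherence to wearing the monitors will be assessed by examining the proportion of participants providing valid accelerometer data across a range of valid days". It reports how many people wore the monitor, not how active they were. Quantitative data analysis says that baseline and follow-up will be described and that no inferential statistics are planned; it sets no other accelerometer population. Table 3 has the research team fit the follow-up monitor at the 11th or 12th session. Table 1 lists among the primary feasibility measures: "Number of patients who refuse, drop out and the reasons for refuse and drop out".

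**The concern.** A baseline summary normally describes the people who were randomised. Here, entry to it depends on something that happens after randomisation: providing a second valid week about six weeks later. A complete baseline week is set aside if that second week is absent or short.

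Two things are at stake. First, Sample size and recruitment target says that the trial should supply data for planning future trials. A baseline mean and SD from people who stayed and wore the monitor twice need not match those of the people a future trial would randomise. Second, the selection could differ by arm. The stated occasion for fitting the follow-up monitor is a late PR session, and control participants attend no sessions, so continued attendance may affect follow-up wear in one arm only.

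**Working it through.** **Step 1: what the text fixes.** The rule covers all reported group averages, and Table 3 makes validity at both time points part of what a file is. A valid baseline week alone is not a valid file. Neither the wear-adherence proportions nor the general statement on descriptive statistics restores activity levels for those with baseline data only. This is a stated rule, not a detail left to a fuller document.

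**Step 2: how many baseline records are affected.** The article states no figure to reproduce. Input from the article: N = 50, 25 per arm. Assumed, because the article gives neither: d, the share with no follow-up wear, and w, the probability of valid wear in a period, taken as independent between periods.

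- Valid baseline files: N × w
- Entering the averages: N × w × (1 − d) × w
- Share of valid baseline files unused: 1 − (1 − d) × w

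| w | Valid baseline | Kept, d = 10% | d = 20% | d = 30% | d = 40% | Share unused, d = 10% to 40% |
|---|---|---|---|---|---|---|
| 1.0 | 50 | 45.0 | 40.0 | 35.0 | 30.0 | 10% to 40% |
| 0.9 | 45 | 36.5 | 32.4 | 28.3 | 24.3 | 19% to 46% |
| 0.8 | 40 | 28.8 | 25.6 | 22.4 | 19.2 | 28% to 52% |

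Taking d = 20% and w = 0.9, 45 − 32.4 = 12.6 valid baseline records are unused. Of these, 45 × 0.20 = 9.0 come from people with no follow-up wear, and 45 × 0.80 × 0.10 = 3.6 from people who stayed but wore the monitor too little.

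**Step 3: how far the baseline mean could move.** If those lost differ from those kept by δ SD at baseline, the mean of those kept differs from the mean of all by d × δ. For δ from 0.25 to 0.8, this is 0.03 to 0.08 SD at d = 10% and 0.10 to 0.32 SD at d = 40%. The sign depends on who leaves.

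**Step 4: an illustration by arm.** Assume w = 0.8, loss of 30% in PR and 10% in control, and δ = 0.5.

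- Valid baseline per arm: 25 × 0.80 = 20
- Kept: PR 25 × 0.80 × 0.70 × 0.80 = 11.2; control 25 × 0.80 × 0.90 × 0.80 = 14.4
- Shift from drop-out alone: PR 0.30 × 0.5 = 0.15 SD; control 0.10 × 0.5 = 0.05 SD; gap 0.10 SD
- Shift if everyone excluded, short wearers included, differs by 0.5 SD: PR (1 − 0.70 × 0.80) × 0.5 = 0.22; control (1 − 0.90 × 0.80) × 0.5 = 0.14; gap 0.08 SD

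For scale, the chance standard error of a difference in arm means is √(1/20 + 1/20) = 0.32 SD with 20 per arm, and √(1/11.2 + 1/14.4) = 0.40 SD with the numbers kept.

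**The case against.** The matched set suits the stated purpose. Secondary outcomes says that baseline is compared with post-intervention to describe changes in health. Keeping both averages on the same people makes their difference the mean within-person change. That stands, and it is why the matched set should remain. Separate sets used as the only averages would mix change with drop-out, and a follow-up average would still be selected on retention.

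The consequences are also limited. Accelerometry is one of many secondary measures, nothing is tested, and the article does not name activity as a future primary outcome. Drop-out numbers and reasons are collected. The baseline activity questionnaire and walking tests carry no both-time-points restriction, so there is other information on those who leave. All of this stands and keeps the point minor. It does not supply accelerometer levels for everyone with a valid baseline week.

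A reader might infer that everyone who withdraws loses their baseline record. The article does not support this: it lists session attendance and attendance at follow-up as separate parts of completion, and someone who stops PR but provides a valid follow-up week is kept.

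A reader might also infer that the reported baseline will overstate activity, or that the arms will lose the balance given by randomisation. The rule makes differential selection possible, but the article does not show which way or how far it would go. The 0.10 SD gap in the illustration rests wholly on assumed rates and is about a quarter to a third of the chance standard error.

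**Conclusion.** The point holds as a minor reporting weakness. That valid baseline records are left out of the baseline mean and SD follows from the text whenever anyone lacks a valid follow-up week. Only the extent is uncertain: 10% to 52% of valid baseline records over the assumed ranges, with independent wear in the two periods. Selection could differ by arm because of how follow-up fitting is tied to PR sessions, but its direction and size cannot be determined from the article. No effect estimate or test depends on it. The practical loss is a baseline description that may not carry over to those a future trial would randomise, and no sight of whether those lost were more or less active at the start.

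**What to change.** - Apply the criterion of at least 4 days of at least 8 hours at each time point separately, so that a valid baseline file is defined on its own. Amend the 'Valid file' row of Table 3 and the matching sentence in Physical activity.
- Report baseline mean, SD and n by randomised arm for everyone with a valid baseline file.
- Keep the both-time-points set for the baseline-to-follow-up comparison and for within-person change. Beside it, show the baseline activity and n of those excluded from it, by arm.

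The cost is a few extra descriptive rows from data already collected. No imputation, modelling or testing is needed, so the rest of the plan is unchanged. The downside is that the two sets contain different numbers of people. Each table should label its set, so that the difference between the full baseline average and the matched follow-up average is not read as change.

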### Procedure

Eligible participants will be informed verbally about the study by the medical officers of the Central Chest Clinic. After receiving a study information sheet, potential participants will be contacted to arrange an appointment, if they wish to take part. An opportunity to ask questions will be provided. If willing to take part in the study, they will be asked to provide written informed consent. Information regarding the interest of participation in the study will be taken as field notes. Baseline outcome measures will be assessed. After baseline data collection, participants will be randomised (1:1) into two groups. One group will receive usual care and PR and the other group will receive only usual care which consists of pharmacological treatment and brief information about disease condition, medication and inhaler techniques. Experiences of the participants and PR deliverers regarding the acceptability and feasibility of PR will be explored in interviews and focus groups during phase 3 of the study. Participants who did not complete the PR will be asked to take part in a drop-out interview and information provided freely by the participants will be collected as field notes.

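### Table 3 times accelerometer wear by PR-arm events, so follow-up fitting is undefined for controls and for anyone absent from sessions 11 and 12, and one supervised session can fall inside the free-living week

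*Protocol article*

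**What the plan says.** The *Physical activity* section asks participants to wear the monitor "for 7 days prior to attending PR (baseline) and for the 7 consecutive days prior to their discharge assessment (follow-up"). It presents Table 3 as the complete account of the accelerometer methods.

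In Table 3:
- **Deployment method, baseline:** "Fitted by research team on day 0 (baseline PR assessment").
- **Deployment method, follow-up:** "Fitted by research team day 0 (11th/12th session").
- **Initialisation:** "stop time based on date of first PR class (baseline) and data of discharge assessment (follow-up").
- **Requested days of wear:** days 1 to 7, described as free living.
- **Valid day and valid file:** at least 8 h of waking wear, on at least 4 days, at each of the two time points.
- **Missing data:** no modelling or imputation.

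Elsewhere, *Usual care* excludes PR and any exercise recommendation. *Procedure* states "After baseline data collection, participants will be randomised (1:1) into two groups", and *Patient allocation, concealment and blinding* says that participants learn their group once baseline assessments are complete. Table 2 lists accelerometry at baseline and post intervention. The Abstract says that both groups are assessed after PR is completed.

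**The concern.** Accelerometry is an outcome of a two-arm trial, but two of the events that time it, the first class and the 11th/12th session, belong to the PR arm. For 25 of the 50 participants those events do not exist, and no substitute date is given.

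Within the PR arm, the choice between two sessions decides whether the recorded week contains supervised exercise. The link to attendance also means that people who stop coming have no stated fitting day.

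Three things are at stake:
- the descriptive comparison of activity between arms;
- the planned estimate of time spent at the prescribed walking intensity, since the programme includes walking at prescribed speed;
- the completeness and adherence figures for the monitor. Table 1 counts data completeness and accuracy among the primary feasibility measures, and the *Physical activity* section plans to report the proportion of participants with valid wear.

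**Working it through.** **The plan's own figure.** The requested window is given as 10 080 epochs of 60 s. 7 days × 24 h × 60 = 10 080, so the window is exactly seven full days after the fitting day.

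**Inputs.** 12 sessions in 6 weeks (Abstract); about 1 h of exercise in a session of about 2 h (*Trial interventions*); 25 per arm (*Sample size and recruitment target*); at least 4 valid days of at least 8 h (Table 3). Session weekdays are not given, so alternating gaps of 3 and 4 days are assumed.

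**Sessions inside follow-up days 1 to 7.** 12 / 6 = 2 sessions a week. Counting the first class as day 0, session 11 falls on day 35 and session 12 on day 38 or 39, depending on which gap comes first.

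| Fitted at | Days 1–7 of wear cover | Supervised sessions inside | Day 8 of wear |
|---|---|---|---|
| Session 11 (day 35) | days 36–42 | 1 (session 12) | day 43 |
| Session 12 (day 38 or 39) | days 39–45 or 40–46 | 0 | day 46 or 47 |

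The overlap does not depend on the exact spacing: session 12 is inside the window whenever it follows session 11 by one to seven days. Table 3 has no rule that removes session time.

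**Size of one included session.**
- Over 7 valid days: 60 / 7 = 8.6 min/day, which is 60 / (7 × 480) = 1.8% of the minimum valid wear time.
- Over 4 valid days, if the session day is one of them: 60 / 4 = 15 min/day, which is 60 / (4 × 480) = 3.1%.

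These are gross figures. They count the whole exercise hour, part of which is resistance work, and subtract nothing for activity displaced that day.

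**Who has no follow-up fitting day.** Usual-care participants, and any PR participant who attends neither session 11 nor session 12. The second group can include someone who attended sessions 1 to 10 and came to the follow-up evaluation. The *Acceptability* section counts that person as a completer, because 10 of 12 sessions plus the evaluation is enough. If such a person is not fitted, the both-time-points rule without imputation removes them from the group averages.

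**Baseline.** Fitting happens at a visit that both arms share, and days 1 to 7 run from that visit. Only the end of recording refers to the first PR class, which has a date only for people allocated to PR. Yet baseline data are due before randomisation. The same section places the activity questionnaire explicitly before randomisation but does not say so for the monitor. The text therefore does not settle whether the seven days finish before allocation is known.

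**Device count (separate and minor).** 20 devices × 6 deployments = 120 wears. 50 participants × 2 wears = 100, or 100 / 20 = 5 per device.

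**The case against.** The strongest reply is that this is a condensed article about a feasibility trial. *Data collection* refers to standard operating procedures that are not shown. Control timing is unspecified, not stated to differ. Accelerometry is one of many secondary outcomes, and *Quantitative data analysis* rules out inferential statistics, so no error rate or sample size rests on it. The overlap is limited to one session, at follow-up, and only when fitting is at session 11.

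These points stand as limits on the size of the problem. They do not remove it, because Table 3 is more than silent: it states a fitting rule that cannot be applied to half the trial and that gives two different windows in the other half.

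A reader might infer more than the text supports:
- **That controls and drop-outs never have a discharge assessment or a first class.** The Abstract gives both groups a post-programme assessment; only the label is PR-specific. A drop-out who started PR did have a first class.
- **That the baseline week falls after allocation.** Fitting is at the shared baseline visit, and allocation is disclosed after baseline assessments. A post-allocation week is possible, not shown.
- **That 5 to 10 of the 25 PR participants would go unfitted.** This comes from assuming 60–80% completion (25 × 0.2 = 5; 25 × 0.4 = 10). But a non-completer who missed three earlier sessions can still be fitted at session 11 or 12, and a completer can miss both. The number cannot be derived from the document.

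**Conclusion.** The point holds in a limited form. The follow-up fitting rule is undefined for usual care and for anyone absent from sessions 11 and 12. It also produces a non-uniform week in the PR arm, with either zero or one supervised session: 8.6 min/day over 7 days, up to 15 min/day over 4. The validity rule then excludes early leavers from the group averages. The baseline stop conflicts in spirit with baseline collection before randomisation, without proving that the week is contaminated by knowledge of allocation.

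The consequence is confined to a secondary, descriptive outcome and to the monitor-completeness data used to judge feasibility. It deserves correction before recruitment but does not threaten the primary outcome as a whole. The conclusion assumes the 12-session, 6-week schedule, which the protocol leaves open to discussion in phase 1, and roughly even spacing of sessions. The document gives no reason to re-time the other post-intervention measures on this account.

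**What to change.** 1. **Follow-up.** Fit the monitor for every randomised participant in both arms, whatever their attendance, at one common time after randomisation that falls after the last scheduled session. Days 1 to 7 then contain no supervised session. If that timing is unworkable, keep a common anchor for both arms and exclude session time from the data by a stated rule.
2. **Baseline.** End recording at day 7 after the baseline visit and randomise only after that week. Remove the first PR class as an anchor.
3. **Diet diary.** Keep it with the monitor at both time points, since the plan says that the two coincide.
4. **Device count.** Reconcile six deployments per device with 50 participants and two wears each, or state who else will wear the devices.

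**Cost.** Changes to Table 3, the *Physical activity* text and the visit windows, with no new equipment. Randomisation and follow-up each move by about a week. Controls also need a fitting contact about a week before their assessment, which the article does not describe at present.
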